### 2.9. Recruitment and Timeline

The project presentation by the principal investigator to the health personnel of the Oncology Service (HULP), regular visits for nutritionists to the day hospital to explain the project to the patients who attended chemotherapy, recruitment of the Monographic Cancer consultation by physicians of the Clinical Nutrition and Dietetics Unit (HULP), reviewing the patient’s medical history, a recruitment posters in patient waiting rooms are part of strategies for achieving adequate participant enrollment to reach target sample size.

The time schedule of enrollment, interventions, assessments, and visits for participants are shown in the schematic diagram (Figure 2).

### 2.10. Sample Size

The sample size is to be established by the researchers owing to the exploratory nature of the study and because there are no previous studies using miraculin-based supplements in cancer patients. At the end of this pilot and to assess the validity of the results, a statistical power calculation will be performed. The obtained results will serve as a basis for establishing the number of participants needed to carry out subsequent efficacy studies.

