## Abstract

Taste disorders are common among cancer patients undergoing chemotherapy, with a prevalence ranging from 20% to 86%, persisting throughout treatment. This condition leads to reduced food consumption, increasing the risk of malnutrition. Malnutrition is associated not only with worse treatment efficacy and poor disease prognosis but also with reduced functional status and quality of life. The fruit of *Synsepalum dulcificum* (Daniell), commonly known as miracle berry or miracle fruit, contains miraculin, a taste-modifying protein with profound effects on taste perception. The CLINMIR Protocol is a triple-blind, randomized, placebo-controlled clinical trial designed to evaluate the regular consumption of a food supplement containing a miraculin-based novel food, dried miracle berry (DMB), on the taste perception (measured through electrogustometry) and nutritional status (evaluated through the GLIM Criteria) of malnourished cancer patients under active antineoplastic treatment. To this end, a pilot study was designed with 30 randomized patients divided into three study arms (150 mg DMB + 150 mg freeze-dried strawberries, 300 mg DMB, or placebo) for three months. Throughout the five main visits, an exhaustive assessment of different parameters susceptible to improvement through regular consumption of the miraculin-based food supplement will be conducted, including electrical and chemical taste perception, smell perception, nutritional and morphofunctional assessment, diet, quality of life, the fatty acid profile of erythrocytes, levels of inflammatory and cancer-associated cytokines, oxidative stress, antioxidant defense system, plasma metabolomics, and saliva and stool microbiota. The primary anticipated result is that malnourished cancer patients with taste distortion who consume the miraculin-based food supplement will report an improvement in food taste perception. This improvement translates into increased food intake, thereby ameliorating their nutritional status and mitigating associated risks. Additionally, the study aims to pinpoint the optimal dosage that provides maximal benefits. The protocol adheres to the SPIRIT 2013 Statement, which provides evidence-based recommendations and is widely endorsed as an international standard for trial protocols. The clinical trial protocol has been registered at the platform for Clinical Trials (NCT05486260).

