Previous studies have shown the potential of miracle fruit for treating taste disorders. A pilot clinical trial involving 23 patients with dysgeusia derived from chemotherapy treatment demonstrated that the consumption of this berry was safe, and 30% of patients showed an improvement in taste after two weeks of treatment [21]. Another pilot trial conducted two years later on eight patients who experienced taste disturbances after chemotherapy treatment showed that all patients demonstrated improvements in taste, with five patients reporting the disappearance of the metallic taste after supplementation with the fruit [22].

Despite the absence of substantial clinical evidence, prior uncontrolled pilot studies have hinted at the potential of using miracle fruit as a natural dietary supplement, presenting a promising nutritional strategy for managing dysgeusia. The current pilot study aimed to generate clinical evidence on the beneficial effect of the miraculin-based food supplement, containing the miracle fruit extract DMB, on taste disorders. Furthermore, the study sought to explore the interplay between this impact and the enhancement of patients’ nutritional status, employing a rigorous design and methodology. A comprehensive outline of the study’s protocol is provided in this article, adhering to the SPIRIT 2013 Statement (Supplementary Material File S1). This statement, recognized as an international standard for trial protocols (https://www.spirit-statement.org/spirit-statement/, accessed on 20 October 2023), offers evidence-based recommendations for the structure of clinical trial protocols.

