### 2.6. Treatments

Each intervention group will be integrated by 10 randomly assigned patients to one of two DMB dosages or placebo. The first arm will have 150 mg of DMB equivalent to 2.8 mg of miraculin + 150 mg of freeze-dried strawberries per orodispersible tablet; the second arm will have 300 mg of DMB equivalent to 5.5 mg of miraculin; and the third arm will contain 300 mg of freeze-dried strawberries per orodispersible tablet as placebo. The three treatments are isocaloric (Table 1). The subjects will be provided with as many tablets as necessary to complete the 3-month intervention period during recurring scheduled visits to the HULP.

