### 2.13. Statistical Methods

A preliminary study to identify out-of-range values or outliers will be performed. Outliers will be considered those that are greater than the value of the means ± 2 standard deviations. A qualitative descriptive analysis of data will be performed in absolute and relative frequencies and percentages. Quantitative data will be presented as the means ± standard deviations (SD), medians, ranges, percentiles, and percentages. The normality of distribution for each variable will be determined using Kolmogorov–Smirnov and Shapiro–Wilk tests. Levene’s test will be used to evaluate the homogeneity of variances. Parametric or nonparametric tests will be performed depending on whether the variables are normally distributed.

A multivariate analysis of covariance (MANCOVA) for repeated measures will be used to analyze the relationship between a dependent variable and multiple independent variables while controlling for the effects of one or more covariates. A separate analysis of covariance (ANCOVA) on each independent variable controlling for the effects of the covariates will be carried out.

A general linear model (GLM) will be used to model the linear relationship between a dependent variable and one or more independent variables (including continuous, categorical, and binary data). The analysis of the qualitative variables and percentages will be carried out through chi-square (χ^2^) or Fisher’s F analysis depending on the variable sample size.

Specific statistical and bioinformatic software will be used for metabolome, microbiome, and metagenome analyses. This includes PCA, OPLS-DA, analysis of metabolic pathways with mummichog (https://shuzhao-li.github.io/mummichog.org/, accessed on 1 October 2023) and GSEA, PERMANOVA, etc., using the R Project for Statistical Computing. R (https://www.r-project.org/, accessed on 1 October 2023).

Double-sided tests will be applied when needed, and a *p*-value < 0.05 will be considered statistically significant. Data will be analyzed using IBM SPSS Statistics for Windows, version 21.0 (IBM Corp., Armonk, NY, USA) and the R Project for Statistical Computing. R is available as Free Software under the terms of the Free Software Foundation’s GNU General Public License in source code form (https://www.r-project.org/ (accessed on 1 October 2023)).

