Numerous studies carried out in recent years using metagenomic techniques indicate that diet is a powerful agent involved in the establishment of specific microbiota, both in the oral cavity and in the colon [167]. In the present study, we addressed changes in the saliva and stool microbiota in cancer patients. Treatment with DMB and the increase in salivation related to some of its active compounds, such as some amides, as well as the change induced in food intake as a consequence of the improvement of taste and smell alterations, should result in relevant changes both in the salivary microbiome, which should be closer to that of the healthy subject, and in the bacterial pattern of the feces, indicative of the microbiome of the distal colon. Therefore, an improvement in the dysbiosis observed in both saliva and intestine [120,121,122,123,124,125,126,127,128,129] is expected in patients supplemented with miraculin.

One disadvantage of clinical trials is the potential decrease in the number of patients, which may be further reduced due to dropouts throughout the study. However, the primary objective of the pilot clinical trial is to comprehensively assess various parameters affected in cancer patients, who are susceptible to improvement through regular consumption of the miraculin-based food supplement.

The outcomes of this pilot clinical trial are anticipated to demonstrate whether the regular consumption of a miraculin-based food supplement, whose active principle is the miracle berry extract DMB, has a positive effect on taste distortion and the nutritional status of malnourished cancer patients undergoing active antineoplastic treatment and to determine the dosage at which maximum benefits are achieved.

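### A power calculation made after the trial cannot show whether its results are valid, and about 10 patients per arm cannot determine the best dose

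*Protocol article*

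**What the plan says.** Section 2.10 gives no calculation for the sample size: "The sample size is to be established by the researchers owing to the exploratory nature of the study". The Abstract says that "a pilot study was designed with 30 randomized patients divided into three study arms", and section 2.6 adds: "Each intervention group will be integrated by 10 randomly assigned patients".

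Section 2.10 then sets out what happens after the data are in: "At the end of this pilot and to assess the validity of the results, a statistical power calculation will be performed". It goes on: "The obtained results will serve as a basis for establishing the number of participants needed to carry out subsequent efficacy studies".

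On dose, section 6 says that the outcomes are anticipated "to determine the dosage at which maximum benefits are achieved", and the Abstract states a similar aim.

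For the primary outcome (change in electrogustometric threshold from v0 to v3), section 2.7 gives only the expected direction. The article states no clinically important difference, SD of change or target power.

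**The concern.** Two statements claim more than the design can deliver.

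The first is the purpose given to the power calculation. Validity depends on randomisation, blinding, measurement, missing data and the analysis. Power describes how often a design would detect a given difference. It does not tell a reader whether a result already obtained can be trusted. If power is computed at the observed effect, it carries no information beyond the p-value. A null pilot could then be put down to low power whatever the truth.

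The second is the dose claim. With three arms of 10 and heavy dropout, the interval for the difference between doses will be wide. A reader told that the best dose had been determined could carry that dose into an efficacy trial on very little evidence.

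**Working it through.** **Inputs**

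- Planned size: 30 in total, 10 per arm (Abstract, section 2.6). Alpha is 0.05 (section 2.13), taken as two-sided.
- Section 5: 31 randomised, 10 dropouts, 21 completers.
- Completers per group, from the percentages of women in Table 3: 62.5% = 5/8, 33.3% = 2/6, 85.7% = 6/7. Check: 13/21 = 61.9%, as section 5 states.
- Baseline electrogustometry (Table 3): 17.16 ± 12.46, 20.5 ± 15.88 and 19.29 ± 15.71 dB.
- SD of change: not stated, so assumed below.

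**The plan's own figures.** N = 30 cannot be reproduced, because no effect, SD or power is given. As a check on the group sizes, a one-way ANOVA of the three baseline values with n = 8, 6 and 7 gives F = 0.095 and p = 0.910. Table 3 states 0.909.

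**Step 1: power at the observed effect.** For two arms of 10 (18 df), take t_obs = t(1 − p/2; 18). Set the true standardised effect to t_obs × √(2/10), so that the noncentrality equals t_obs. Power is then the probability that a noncentral t exceeds 2.101 in absolute value.

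| Observed p | t_obs | Power, 10 v 10 | Power, three-arm ANOVA, N = 30 |
|---|---|---|---|
| 0.50 | 0.69 | 10% | 16% |
| 0.20 | 1.33 | 24% | 33% |
| 0.05 | 2.10 | 51% | 58% |
| 0.01 | 2.88 | 78% | 81% |

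Only p and the arm sizes enter. At 8 v 6 the pairwise values are 10%, 24%, 52% and 80%. Any pairwise p above 0.05 gives power below about 51% or 52%.

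**Step 2: precision of a pairwise difference.** Half-width in SD units = t(0.975; n1 + n2 − 2) × √(1/n1 + 1/n2).

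- 10 v 10: 2.101 × 0.447 = 0.94
- 8 v 6: 2.179 × 0.540 = 1.18

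Table 3 does not say which group received which dose. The other completer pairings give 1.12 (8 v 7) and 1.22 (6 v 7).

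**Step 3: conversion to dB.** Pooled baseline SD = √[(7 × 12.46² + 5 × 15.88² + 6 × 15.71²)/18] = 14.6 dB. The SD of change equals SD × √(2(1 − r)) when the variances are equal, so it is 14.6 dB only if the correlation r between visits is 0.5. That is an assumption, and a range of 10 to 20 dB is also shown.

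| SD of change | Half-width, 10 v 10 | Half-width, 8 v 6 |
|---|---|---|
| 10 dB | 9.4 dB | 11.8 dB |
| 14.6 dB | 13.7 dB | 17.2 dB |
| 20 dB | 18.8 dB | 23.5 dB |

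For scale, the weighted baseline mean is (8 × 17.16 + 6 × 20.5 + 7 × 19.29)/21 = 18.8 dB.

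**Step 4: power to separate the doses.** For a true difference of 0.5 SD, power is 19% at 10 v 10 and 14% at 8 v 6. The difference detectable with 80% power is 1.32 SD and 1.65 SD respectively.

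**Step 5: allowance for an uncertain pilot SD.** The one-sided 80% upper limit is SD × √(df/χ²(0.20; df)). At the planned 27 df the factor is 1.14, which multiplies n by 1.30. At the 18 df left by 21 completers it is 1.18, which multiplies n by 1.40.

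**The case against.** **Section 2.10 does not say at which difference power will be computed.** This stands. Power at an external target difference, using the pilot SD, would not be a function of the p-value. Step 1 is therefore conditional. But no such difference is named, and even that power would describe the design and not the validity of the results.

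**A declared pilot needs no formal sample size, and no randomisation, endpoint or test depends on the calculation.** This also stands, and it lowers the weight of the point.

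**A dose can be chosen without a significance test, by taking the arm with the better mean.** If one dose is truly better by 0.5 SD, that picks it about 87% of the time at 10 v 10 and 82% at 8 v 6. At 0.2 SD the figures are 67% and 64%. The article states no such selection rule, however, and its wording promises a determination, not a provisional choice. Nor does it link the dose aim to the power calculation; that weakness comes from the arm sizes alone.

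A reader might infer three stronger points, which the article does not support:

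- *The pilot cannot be used to size the next trial.* Section 2.10 refers to the obtained results in general. It names neither the observed effect nor the power figure, and a pilot's SD and dropout rate are legitimate inputs.
- *The stated lack of previous studies contradicts the Introduction*, which reports: "A pilot clinical trial involving 23 patients with dysgeusia derived from chemotherapy treatment demonstrated that the consumption of this berry was safe". Section 2.10 speaks of miraculin-based supplements, whereas the Introduction describes patients taking the fruit. Section 6 calls those pilots short and unblinded, without validated taste tools. At most the wording is loose.
- *The outlier rule will shrink the pilot SD.* Section 2.13 says: "Outliers will be considered those that are greater than the value of the means ± 2 standard deviations". That defines outliers. It does not say that they will be deleted.

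**Conclusion.** The point holds in two parts, and both should be fixed. Using a post-trial power calculation to judge validity is wrong as written. On the natural reading, at the observed effect, it repeats the p-value: 51%, 24% and 10% for p = 0.05, 0.20 and 0.50 at 10 per arm. The promise to identify the best dose also exceeds the design. The half-width is 0.94 SD at the planned 10 v 10 and 1.18 SD at 8 v 6.

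The SD-unit figures rest only on the arm sizes and a two-sample t interval. The dB figures also rest on the assumed SD of change, and the completer figures on group sizes inferred from Table 3. That the pilot has no prior power calculation is not part of the criticism.

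**What to change.** 1. In section 2.10, delete the post-trial power calculation and its stated purpose. Report each between-arm difference with its 95% confidence interval, and interpret the pilot by those intervals.
2. State that the efficacy trial will be sized from a clinically important difference fixed in advance, the pilot's dropout rate, and an upper confidence limit of the pilot SD of change. Compute that limit on the degrees of freedom actually obtained, for example the one-sided 80% limit: 1.14 × SD at 27 df, 1.18 × SD at 18 df.
3. In the Abstract and section 6, restate the dose aim as exploratory estimation of the difference between doses, with its confidence interval.

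These are wording changes and need no new data. The claims become more modest. Using the upper limit in place of the point estimate of the SD raises the next trial's planned n by about 30% at 27 df or 40% at 18 df.

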### 2.11. Assignment of Interventions

Study patients are to be randomized into one of three study arms using computer-generated random numbers listed (in blocks of six) as a method of generating the allocation sequence. This sequence is generated by the Biostatistics Unit (HULP). At the same time, a second list will be filled considering the most prevalent cancer types (head and neck, colorectal, lung, etc.). In this list, the ID patient number is noted in triplicate based on the randomly assigned treatment and cancer type. This second list ensures the balance of each type of cancer in each of the intervention groups. The allocation sequence is provided in a separate document that is unavailable to those who enroll participants or assign interventions. To implement the allocation, the sequence is sequentially numbered in opaque and sealed envelopes by a different researcher who enrolls and assigns participants to interventions. The envelope with the patient’s randomization is to be opened by the nutritionist when the patient signs their informed consent at visit 1.

Researchers, trial patients, care providers, outcome assessors, data analysts, and the promoter are blinded after assignment to interventions. The blinding of the study is achieved by the presentation and identical characteristics of the product to be consumed. The chewable tablets, both the miraculin-based food supplement and placebo, are similar in appearance (Figure 3). These are packaged in white opaque bottles with 30 tablets, uniquely identified by a lot number (L01, L02, L03). The labeling identified the clinical trial name and HULP code, lot and serial number, use and dosage, as well as the expiration date and storage requirements. It is also identified with a unique barcode for tracking.

The chewable tablets are supplied by the promoter Medicinal Gardens S.L. However, they were produced, labeled, identified, and supplied by Activ Vial^®^ from CSP Aptar Technologies, Auburn, AL, USA. This company is the only one aware of the allocation until the opening of the blind once the statistical analysis is completed. To maintain blinding, patients will be identified in the database with the ID number and the assigned lot number. Once the study has been completed, the data file will be verified, any protocol violations will be determined, the statistical analysis will be completed, and the codes will be opened.

### 2.12. Data Collection and Management

The study data will be treated following the referenced confidentiality standards and the quality criteria described above. A specific database will be created in Microsoft Office Standard Excel 2013 (Microsoft® Company) using a standardized database creation process. All data collected in the research data collection will be entered by a member of the research team into the original database. This database will be designed with a double-entry system and filters to prevent and detect any type of inconsistency or error. Data will be incorporated based on the ID patient and visit where the results will be collected (vS, v1, v2, v3, v4, v5). The clinical trial Principal Investigator oversaw supervising the database construction. Databases will be stored in the HULP repository within the closed circuit, and RDC will be stored in the nutritionist’s office in a locked filing cabinet.

During the database creation process, a member of the research team will be in charge of notifying the principal investigator of the presence of missing values. These values will be those that for any reason have not been reflected in the RCD by the patient. The member of the research team indicated the affected cells in the database by coloring them yellow with the word “missing”. Once indicated, the sample size of the affected variable will be adjusted for subsequent statistical analysis. In no case will the patient record be deleted, only the missing value that affects the variable.

After incorporating all the data into the database, they will be duly cleaned, avoiding the appearance of symbols (<, >, etc.) that could interfere with the subsequent statistical analysis. The same member of the research team in charge of creating the original database will be in charge of creating a second database in which alphanumeric coding will be given to each variable to guarantee masking during data analysis. If so needed, new variables such as groupings or sums will be created to facilitate comparison between protocol main visits. When the database is finished, the Principal Investigator will oversee sending the Excel file to the Department of Biochemistry and Molecular Biology II (University of Granada) for analysis.

One of the plans to promote participant retention and complete follow-up is the delivery to the end of the trial of the solidarity cookbook “Cooking with Science against Cancer”, where renowned Spanish chefs designed simple dishes with foods that contain nutrients that are protective against cancer [131].

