#### 2.8.8. Tolerance and Adverse Events

Nausea, diarrhea, dysphagia, vomiting, constipation, and abdominal pain are gastrointestinal symptoms that are used to measure product consumption tolerance. However, they are also considered supportive indicators that can impair food intake or absorption, an etiological criterion used for malnutrition diagnosis [23]. Symptoms of intensity, frequency, and duration will be collected in a diary sheet throughout the study and evaluated at every visit, and the percentage change between visits will be compared between treatments. Gastrointestinal disorders will be judged using Common Terminology Criteria for Adverse Events (CTCAE) from the National Cancer Institute [82]. These adverse events will be used to discern the severity of food intake or absorption impairment and evaluate tolerance to the nutritional intervention. CTCAE will be evaluated at the beginning (v1) and end of the intervention (v5), and the percentage change between these two visits will be compared between treatments. Evolution will also be measured on v1, v3, v4, and v5.

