## 5. General Characteristics of the Population

This section presents very preliminary results of the clinical trial. For the present study a total of 62 patients were evaluated for eligibility. Of them, 31 met the selection criteria and were randomized into three intervention groups (Figure 5). During follow-up, there were 10 dropouts, mainly due to the consumption of the supplement distorted the taste of some non-sweet acidic foods (n = 6) and because of the prescription added difficulty to their, already complex, antineoplastic treatment (n = 2). A final sample of 21 patients completed the clinical trial.

The sample was made up of 61.9% women and 38.1% men with a mean age of 59.8 ± 11.65 years old, all of them undergoing active treatment with chemotherapy and taste alteration measured by electrogustometry (Table 3). The average body mass index was 22.37 ± 3.67 kg/m^2^, classifying the patients as normal weight. However, the weight lost in the last 3 months was −7.60 ± 5.76%, with no significant differences between treatment groups. 

The most prevalent type of cancer was colorectal cancer (28.6%) followed by breast, lung, pancreas and liver cancers, each with 9.5%. Fasting glycemic control (105 ± 19 mg/dL) was within the normal reference parameters (74–106 mg/dL). The insulin concentration (12 ± 10 µU/mL) was normal in the entire population (3–25 µU/mL) as well as the lipid profile. All patients had systemic inflammation (CRP > 5 mg/dL). Both vitamins and minerals were found within the reference values except for vitamin D, which means blood concentration (21.25 ± 13.86 ng/mL) was insufficient (range 15–30 ng/mL).

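### The missing-value rule and the repeated-measures MANCOVA treat incomplete patients differently, neither deals with product-linked dropout, and Table 3 describes the 21 completers instead of the 31 randomised

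*Protocol article*

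**What the plan says.** - **Missing values (Section 2.12).** Blank cells are flagged, then "Once indicated, the sample size of the affected variable will be adjusted for subsequent statistical analysis". The rule is limited in the next sentence: "In no case will the patient record be deleted, only the missing value that affects the variable".
- **Model (Section 2.13).** "A multivariate analysis of covariance (MANCOVA) for repeated measures will be used", alongside ANCOVA and a general linear model. The section does not say which of these serves the primary comparison, or how incomplete patients enter any of them.
- **Primary outcome (Section 2.7).** Change in electrical taste threshold from v0 to v3, one month into a three-month intervention, compared between arms.
- **Patient flow (Section 5).** "Of them, 31 met the selection criteria and were randomized into three intervention groups". "During follow-up, there were 10 dropouts", "mainly due to the consumption of the supplement distorted the taste of some non-sweet acidic foods (n = 6"), with 2 more attributed to the added burden of the prescription. "A final sample of 21 patients completed the clinical trial".
- **Tolerance (Section 2.8.8).** For CTCAE grades at v1 and v5, "the percentage change between these two visits will be compared between treatments". The same section also provides for a symptom diary throughout the study, assessment at every visit, and CTCAE at v1, v3, v4 and v5.

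**The concern.** A cell-by-cell rule and a model that needs complete patients select different people from the same database. Under the first, a patient who leaves after v3 still contributes up to v3. Under the second, that patient contributes nothing once later visits are modelled. The article does not say which prevails.

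This matters because the main reason for leaving lies in the same domain as the primary outcome. If those who left responded differently from those who stayed, a completer analysis estimates the effect in patients who accepted the product. Section 2.10 intends the results to size later efficacy studies, and Section 6 intends them to identify the dosage with the greatest benefit, so both would inherit the selection. Section 2.5 adds another route to missing data, since patients who do not keep to the prescribed dose are taken out of the study.

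**Working it through.** **1. Patient count.** Section 5: 31 − 10 = 21, as stated. Lost: 10/31 = 32.3%. Lost for taste distortion: 6/31 = 19.4%. Lost for taste distortion or burden: 8/31 = 25.8%, i.e. 8 of the 10.

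**2. Whom Table 3 describes.** The percentages fix the group sizes.
- Women: 62.5% = 5/8, 33.3% = 2/6, 85.7% = 6/7. The cancer-type entries of 12.5%, 16.7% and 14.3% fit 1/8, 1/6 and 1/7.
- 8 + 6 + 7 = 21, and (5 + 2 + 6)/21 = 13/21 = 61.9%, the figure in the text.
- Age: (8 × 60.13 + 6 × 58.83 + 7 × 60.14)/21 = 59.76 (stated 59.8).
- BMI: (8 × 20.79 + 6 × 23.13 + 7 × 23.53)/21 = 22.37 (stated 22.37).
- No count out of 31 gives 61.9%: 19/31 = 61.3%, 20/31 = 64.5%.

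Table 3 and the accompanying text therefore cover completers only.

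**3. Whether the omitted baseline values should exist.** Section 4.1 places GLIM status and electrogustometry at v0. Sections 2.11 and 4.2.1 place randomisation at v1. These two baseline items should exist for all 31, and Section 2.12 says records are kept. Table 3 thus departs from the article's own rule.

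**4. Unreported denominators.** Radiotherapy in Group 2 is given as 20.00%. With 6 patients the nearest values are 1/6 = 16.7% and 2/6 = 33.3%. It fits 1/5, so n seems to have been reduced for that variable without being shown.

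**5. Ceiling for the longitudinal model.** If v5 is among the modelled visits and complete data are required, at most 21/31 = 67.7% enter, and fewer if a completer missed an intermediate visit.

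**6. Losses by arm.** These are not stated in the text, and the flow diagram is not reproduced in the copy reviewed. If blocks of six gave a 10/10/11 split, Groups 1, 2 and 3 lost 2 or 3 (from 8 completers), 4 or 5 (from 6) and 3 or 4 (from 7). Every group, placebo included, would have lost someone. Table 3 does not say which group is which, and reasons are not given by group.

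**7. Possible bias, on assumptions that are not in the documents.** Let a share f of the two active arms (about 21 of 31 patients) leave for product reasons, with outcomes worse by d SD than the rest. The completer mean then overstates the active-arm mean by f × d.
- All 6 in the active arms, d = 0.5: 6/21 × 0.5 = 0.14 SD.
- All 8 in the active arms, d = 1.5: 8/21 × 1.5 = 0.57 SD.
- If d = 0, or the dropouts are spread evenly with the same gap in each arm, the bias in the contrast is about zero.

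**The case against.** Several stronger readings are tempting, and the documents do not support them.

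- **That the missing-value rule produced the 21.** A reader might infer this from the reduced n. Section 2.12 keeps every record and concerns cells left blank, so followed literally it would give a baseline table of up to 31.
- **That the primary comparison is confined to completers.** It ends at v3, dropout timing is not given, and Section 2.13 does not tie the MANCOVA to it. Anyone leaving after v3 could still contribute. Dropping incomplete patients is a property of the classical method, not something the article states.
- **That dropout is shown to depend on arm and outcome.** Placebo contains no miraculin (Table 1), so taste distortion plausibly fell mainly on the active arms, but that is inference. Disliking the altered taste of some acidic foods also does not establish a worse electrical threshold in dB.
- **That tolerance is observed only in completers.** Diary and interim-visit data are collected, and Section 2.2 has withdrawing patients asked about adverse events. Only the v1 to v5 contrast is restricted.
- **That the harm can be priced as a wider interval.** Seven rather than ten patients per arm gives a 95% half-width of 17.0 rather than 13.7 dB (17.0/13.7 = 1.24, or 24% wider). That uses the baseline SD of 14.58 dB pooled from Table 3, not the SD of change. It also measures the loss of patients, which no model recovers.

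It is also fair to say that Section 5 is labelled very preliminary, that the trial is an exploratory pilot, and that an analysis plan not shown may define the analysis sets. This narrows the point but does not remove it. The missing-value rule and the model are both stated choices, and the completer table is already published as the characteristics of the population.

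**Conclusion.** The point holds in a limited form. The article's cell-wise rule and its repeated-measures MANCOVA, taken in its classical form, do not agree on incomplete patients. Neither deals with dropout linked to the product. Ten of 31 randomised patients (32%) were lost, 6 of them (19%) for taste distortion, so informative dropout is plausible but not demonstrated. A complete-case model through v5 could use at most 68% of those randomised. The effect on the v0 to v3 comparison cannot be determined from the article. The range of 0.14 to 0.57 SD above is only an illustration of possible size and rests wholly on its assumptions.

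That Table 3 and the Section 5 text describe completers is firm: three summary figures reproduce from 8, 6 and 7 patients, and the percentage of women cannot come from 31. The p-values in that table therefore do not compare the randomised groups. The v1 to v5 CTCAE contrast omits those who left before v5, although other tolerance data exist for them.

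**What to change.** - **Analysis set.** Analyse all randomised patients in the arm assigned.
- **Model.** Replace the repeated-measures MANCOVA with a linear mixed model (arm, visit, arm by visit, baseline value, correlated visits within patient) that uses every available visit, with the v3 contrast as primary. It assumes that missingness is explained by the observed data. A patient with no post-baseline value adds nothing to it, hence the next item.
- **Sensitivity analysis.** One analysis in which patients who left for taste distortion are given no improvement, or placebo-like values.
- **Reporting.** Dropouts by arm, visit and reason; Table 3 for all 31 with n shown per variable.
- **Tolerance.** Worst grade up to last contact, plus the proportion stopping for product reasons, in all who took a tablet.

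The cost is some wording and a little more analysis work. No new data are needed, and SPSS and R, both already named in Section 2.13, fit the model. By the article's account sample analyses are still under way and the codes open only after the statistical analysis, so the change can still be made blind. The price to accept is that the estimated effect may become less favourable.
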